### Patient identification and consent process

Patients will be recruited from the Liver Unit at NuTH. After receiving standard of care treatment for HCC, patients typically undergo post-treatment imaging (CT or MRI scan) and attend a follow-up appointment at the specialist liver cancer clinic. The treating physician will identify potential patients ahead of the follow-up appointment by reviewing post-treatment imaging reports and medical records, which are routinely sent for review. A member of the clinical care team will also review the HUNTER trial registry (ISRCTN16680540) to identify potentially eligible patients.

Patients that meet the eligibility criteria will be sent a study invitation letter and participation information sheet by mail. At the clinic visit, the treating physician will discuss the study with eligible patients after they have received standard NHS care (i.e. review, examination, and blood tests). If the patient is interested in taking part, a research team member will provide them with more information at the clinic, answer any questions about the study, obtain written informed consent, and collect baseline data. Baseline data will include medical history, sociodemographic information, body mass, height, resting blood pressure, and resting heart rate.

### Preparation procedures

Patients will be offered an ‘induction’ to the intervention after baseline data is collected. The induction will take place either on the same day as the clinic appointment, in the clinic on an alternative day, or during a home visit, depending on patient preference. Offering home visits is a useful strategy to improve recruitment of patients whom live in rural or non-local areas [25].

During the intervention induction, a member of the research team will show patients how to use the Zoom videoconferencing platform (Zoom Video Communications, California, USA) on a tablet and familiarise them with the exercises and equipment to be used in the study. The researcher will initially demonstrate an exercise and then ask the patient to perform the exercise themselves, with technique adjusted if necessary. Patients will also be instructed on how to self-monitor exercise intensity using the Borg 10-point rating of perceived exertion (RPE) scale [26]. Patients will then receive an intervention pack that includes an instruction manual, exercise diary, RPE scale, incremental level resistance bands (TheraBand, Ohio, USA), pedal exerciser (NRS Healthcare, Leicestershire, UK), and a wrist-worn accelerometer (ActiGraph GT9X Linkm, ActiGraph, LLC., Pensacola, FL). The exercise diary will be used to record daily step counts as well as the type, duration, and intensity of exercise completed each day (including the virtual exercise sessions). Patients without Internet access or an appropriate Internet-enabled device will be provided with a 10.4-inch tablet preloaded with the Zoom app and unlimited 4G data for the duration of the study (Samsung Galaxy Tab A7 10.4” 4G tablet) free of charge. It will be made clear to the patient that they will not be held responsible for loss or accidental damage of any of the equipment supplied by the research team. The equipment will be handed to patients in the clinic or sent by post (via a tracked courier/mailing system) if there are any concerns about the patient’s ability to carry the equipment home.

In addition, the researcher will schedule a 15-min, one-on-one, online introductory session on Zoom with each patient before the intervention begins. During the introductory session to Zoom, the researcher will inspect the location of the exercise area, resolve any technical issues, and ask the patient to practise a sample of the exercises to be used in the study in order to reassess technique and RPE, with exercises modified if required. Patients will be emailed a URL to a password-protected virtual Zoom ‘room’ ahead of their first scheduled exercise session. The same password and URL will be used for all the exercise sessions.

### Exercise intervention

Patients will be invited to take part in two virtual exercise sessions per week for 10 weeks. Exercise sessions will comprise a maximum of 10 patients at any one time to allow for adequate safety monitoring and provision of individual feedback. Sessions will be delivered on weekdays in the late morning or early afternoon, which reflects patient preferences identified in our patient and public involvement (PPI) discussions and also avoids early morning exercise when exercise-induced adverse cardiovascular events are more frequent [27]. Exercise sessions will be separated by at least 48 h.

Exercise sessions will involve the option of chair-based or standing-based exercises (within the same session). Whether patients complete chair-based or standing exercises will depend on patient preference and functional ability (assessed by the research team); patients who take > 15 s to perform five sit to stands at baseline, show an inability to stand for 10 s in side by side/semi-tandem/tandem on baseline balance tests, self-report falling within the last 12 months, and/or score < 50% on the Activities-specific Balance Confidence scale (ABC scale), will be restricted to chair-based exercises in weeks 1–4 because of an increased risk of falls [28, 29]. A fall event is defined as ‘when you land on the floor or the ground, or fall and hit objects like stairs or pieces of furniture, by accident’ [30]. If a patient expresses a preference to change to standing or seated exercises after this period, they will be reassessed virtually and permitted to do so if they meet the requirements stated above. We will ask patients to nominate an emergency contact who we will contact if an adverse event occurs during the exercise sessions. In the case of an emergency, the research team will also contact emergency services and terminate the exercise session for all patients. Furthermore, we will encourage patients to have another person in the house when they are taking part in the scheduled exercise sessions, but if this is not possible, we will ask them to remotely ‘check in’ with their nominated contact after completing each exercise session. Patients will be required to have their cameras turned on and be visible during the exercise sessions so that they can be monitored for potential adverse events.

Each exercise session will last 45 min and comprise of a 10 min warm up, 30 min of aerobic and resistance exercises, and a 5 min cool down involving static stretching. The exercises focus on multi-joint movements recruiting major muscle groups in the lower and upper body. The warm up will involve 5 min of a pulse-raising activity (such as seated pedalling) and 5 min of joint mobility exercises. Patients will then perform two sets of four aerobic exercises and two sets of four resistance exercise in a circuit-like manner. Each exercise will be performed for 60 s followed by 60 s of rest; this length of time was chosen to provide an adequate stimulus for adaptation but also provides patients enough time to prepare for the next exercise. Aerobic exercises will include exercises such as seated pedalling, high knee marching, step jacks, side steps, stepping forwards/backwards, and horizontal/vertical punches. Resistance exercises will use body weight and resistance bands as resistance and will include exercises such as chai rises, assisted lunges, horizontal rows, upright rows, overhead presses, wall press-ups, calf raises, rotations, and bicep curls. Each exercise can be modified to be performed in either a seated or standing position. The combination and sequencing of exercises will be varied between the two weekly sessions because our PPI discussions and previous research [20] suggest that older adults taking part in online exercise prefer some level of variation. An example exercise session is presented in Fig. 2.

**Fig. 2 Fig2:**
[figure not shown]
Example of TELEX exercise session. ES, each side

The intensity of exercise will be performed at 3–6 on the Borg 10-point RPE scale, which corresponds to moderate intensity [31] and qualitative descriptions of ‘moderate’ to ‘hard’ [26]. Moderate-intensity exercise has been shown to improve QoL in cancer survivors [11] and is less likely to trigger acute cardiovascular events compared with vigorous-intensity exercise [32]. The use of RPE to guide intensity ensures that the exercise intervention has inherent progression as participants become accustomed to the exercise. Each session will finish with a cool down of static stretching held for 20 s each at the point of ‘slight discomfort’ [31]. The intervention facilitator will document attendance, adverse events, and any noteworthy technical/practical issues that arise during each session.

### Other intervention components

Patients will have the option of contacting a research team member via telephone or email for assistance if they have any questions or experience any issues, such as technical difficulties using the videoconferencing software. No concomitant care or interventions will be prohibited during the trial [24].

Patients will be able to retain their resistance bands and pedal exerciser at the end of the study to allow them to continue exercising at home after the study has finished. Tablets and accelerometers will be returned to the research team at the follow-up visit to the hospital.

### Outcomes

The primary outcome for this study is feasibility of the exercise intervention and study procedures. Measures of physical function, mid-upper arm circumference, objectively measured physical activity, and PROMs will be assessed before and after the 10-week intervention to determine the feasibility of assessing outcome measures. Acceptability of the intervention will be assessed using a mixed-methods approach via monthly online surveys and an exit telephone interview (see Fig. 1).

#### Feasibility

Feasibility outcomes include recruitment rate, retention rate, intervention adherence, intervention fidelity, and safety. The definition and criteria for success for each feasibility outcome are presented in Table 1. Reasons for declining to participate in the study, and reasons for withdrawing from the study after providing consent, will also be recorded in a Consolidated Standards of Reporting Trials (CONSORT) flowchart.

**Table 1 Tab1:** Feasibility outcomes for this study

Outcome	Definition
Recruitment rate	The proportion of eligible patients who are approached and give informed consent to participate
Retention rate^a^	The proportion of patients who consent to take part in the study and complete the FACT-Hep questionnaire at both baseline and 10-week follow-up
Intervention adherence^b^	i) The mean proportion of exercise sessions attended by patients (assessed by attendance records kept by the intervention facilitator) ii) The mean proportion of exercise sessions completed at or above a moderate intensity, assessed via RPE (rating of ≥ 3 on the 10-point scale)
Intervention fidelity	Assessed by a research team member attending a 10% sample of the virtual exercise sessions using a standardised checklist to check whether the sessions are delivered in accordance with the protocol
Safety	The number and type (i.e. serious or non-serious) of adverse events that are related or possibly related to the intervention or study procedures

^a^The Functional Assessment of Cancer Therapy-Hepatobiliary (FACT-Hep) questionnaire was chosen for the assessment of retention rate because this is likely to be our primary outcome for a subsequent randomised controlled trial

^b^Adherence to the intervention will be evaluated only in patients who complete the study, defined as patients who complete the FACT-Hep questionnaire at both baseline and 10-week follow-up

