### Safety reporting

Reporting of adverse events will be conducted in line with NuTH’s policy on adverse event reporting for non-clinical trials of investigational medicinal products (CTIMPs). A member of the research team ([name]) will be responsible for determining the attribution and seriousness of adverse events and ensuring they are appropriately documented. All adverse events will be recorded in the Trial Master File. We will report serious adverse events that are deemed to be related to study participation to the trial sponsor and the relevant research ethics committee. Serious adverse events are defined as any untoward medical occurrence that results in death, is life-threatening, requires unplanned or prolonged hospitalisation, results in persistent or significant disability or incapacity, or results in a congenital abnormality/birth defect. Non-serious adverse events are defined as any untoward medical occurrence that do not fulfil any of the serious adverse event criteria [47]. Information on adverse events will be collected after written consent has been contained up until the 10-week follow-up. Patients enrolled into the study are covered by indemnity for negligent harm through NHS schemes. Newcastle University has insurance to cover for nonnegligent harm arising from the design of the research.

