### Criteria for success

Based on a systematic review of recruitment, retention, and exercise adherences rates in patients with advanced cancer [49], this feasibility trial will be deemed successful if the following criteria are met:≥ 40% of eligible patients provide written consent to take part in the feasibility trial.≥ 70% of patients attend at least 14 out of 20 exercise sessions.≥ 75% of patients complete the FACT-Hep questionnaire at baseline and 10-week follow-up.No serious adverse events are attributable to the intervention or study procedures.

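### The adherence and safety success criteria do not use the quantities Table 1 defines, which leaves the adherence denominator and the causality term open

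*Protocol article*

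**What the plan says.** Feasibility is the primary outcome (Outcomes). The Feasibility section says that Table 1 gives both the definitions and the success criteria. The table as printed gives definitions only; the thresholds stand in Criteria for success.

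- **Adherence, Table 1:** "The mean proportion of exercise sessions attended by patients". Footnote b adds: "Adherence to the intervention will be evaluated only in patients who complete the study", where completing means returning the FACT-Hep questionnaire at baseline and at 10 weeks.
- **Adherence, Criteria for success:** "≥ 70% of patients attend at least 14 out of 20 exercise sessions". No completer restriction is stated.
- **Safety, Table 1:** the number and type of "adverse events that are related or possibly related to the intervention or study procedures".
- **Safety, Criteria for success:** "No serious adverse events are attributable to the intervention or study procedures".
- **Safety reporting:** "We will report serious adverse events that are deemed to be related to study participation", to the sponsor and the ethics committee. One research team member determines attribution.

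The recruitment and retention criteria match their Table 1 definitions.

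**The concern.** The four criteria decide whether this trial counts as a success, and the result is meant to inform the design of a randomised trial. For adherence, the outcome is a mean and the criterion is a share of patients above a cut-off; neither determines the other. The outcome is also limited to completers, and the criterion is not. For safety, the article uses three causality wordings (related or possibly related; attributable; deemed to be related) and does not say how they correspond. With 20 patients and a criterion that allows no events, these differences can reverse the verdict. If they are not settled beforehand, they will be settled by whoever reads the criteria once the data are known.

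**Working it through.** **Inputs.** The target is 20 patients (Sample size). At three eligible patients a week and 30% consent, 26 weeks gives 26 × 3 × 0.30 = 23.4 and 24 weeks gives 21.6, so the article's figure of at least 20 is reproduced. Sessions offered: "two virtual exercise sessions per week for 10 weeks", so 2 × 10 = 20, and 14/20 = 70%. The retention criterion is 75%, so at least 0.75 × 20 = 15 completers are needed to pass it.

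**Step 1: mean against share (n = 20, all completers).** Mean = total sessions attended / (20 × 20). Share = patients with at least 14 sessions / 20.

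- 14 patients at 14 sessions and 6 at none: mean = (14 × 14 + 6 × 0)/400 = 49%; share = 14/20 = 70%. The criterion is met.
- 13 patients at 20 sessions and 7 at 13: mean = (13 × 20 + 7 × 13)/400 = 351/400 = 87.75%; share = 13/20 = 65%. The criterion is missed.

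These are the extremes: the lowest mean with the criterion met and the highest with it missed.

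**Step 2: completers against all enrolled.** Take 15 completers, 13 at 18 sessions and 2 at 10, and five non-completers at 3 sessions each.

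- Completers: share = 13/15 = 86.7%, met. Mean = (13 × 18 + 2 × 10)/300 = 254/300 = 84.7%.
- All enrolled: share = 13/20 = 65%, missed. Mean = (254 + 15)/400 = 67.3%.

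The statistic and the 70% mark are the same; the verdicts are opposite.

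**Step 3: how often the denominator can matter.** Assume that no non-completer reaches 14 sessions. Among all 20, 14 patients must reach the cut-off. Among m completers, 0.70 × m rounded up must do so.

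| Completers | Needed among completers | Counts that pass in completers but fail in all 20 |
|---|---|---|
| 15 | 11 (10.5) | 11, 12, 13 |
| 16 | 12 (11.2) | 12, 13 |
| 17 | 12 (11.9) | 12, 13 |
| 18 | 13 (12.6) | 13 |
| 19 or 20 | 14 | none |

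Completion is defined by a questionnaire and not by attendance, so the reverse is also possible. If 10 of 15 completers and 4 of 5 non-completers reach 14 sessions, completers give 10/15 = 66.7% (missed) and all enrolled give 14/20 = 70% (met).

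**Step 4: safety, wording side by side.** Suppose one serious event is judged possibly related. Under Table 1 it is counted in the safety outcome. Under Criteria for success it fails the trial if *attributable* includes possibly related events, and does not if the word means related only. The text shown does not choose between these readings.

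**The case against.** The strongest reply is that only one adherence rule carries a threshold. Table 1 sets no pass mark for mean attendance, so a mean of 49% fails nothing and a mean of 87.75% passes nothing. Describing attendance by a mean and judging it by a responder cut-off is ordinary practice. This stands. A reader might infer from Step 1 that the mean itself gives a competing verdict, or that the adherence statistic could be chosen after the data are seen. The documents support neither: Criteria for success fixes the statistic and the 70% mark, and a clash with the mean would need a cut-off that appears nowhere. The 49% example also requires the six patients with no attendance to be completers. If they were not, the completers' mean would be 70% and retention would be 14/20 = 70%, so the trial would fail on retention anyway.

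One may also argue that footnote b carries over to the criterion. It may be meant to, but the next criterion in the list, on retention, uses *patients* in a sense that must include non-completers, since otherwise it would always be 100%. The same word would then have two meanings in adjacent lines.

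On safety, restricting the criterion to serious events is a normal threshold, and the inconsistency lies only in the causality term. A reader might infer that a possibly related serious event would go unrecorded. It would not: Table 1 counts it, and Safety reporting has all adverse events entered in the Trial Master File. The *deemed to be related* wording governs notification, under a sponsor policy that is not shown. That a single event can decide the trial follows from any zero-event criterion and does not measure the mismatch.

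**Conclusion.** The point holds in a limited form. Two of the four success criteria are not aligned with the Table 1 outcomes that they are meant to judge. For adherence, the material defect is the unreconciled denominator: with 15 to 18 completers, between one and three possible counts of adherent patients give opposite verdicts, assuming 20 enrolled and no non-completer reaching 14 sessions. The gap between mean and share is a mismatch of definition, not a second verdict. For safety, one undefined word decides whether a possibly related serious event fails the trial. The examples are constructed to show what is possible; they do not estimate how likely it is. This should be corrected because it concerns the decision rules for the primary outcome, but it does not undermine the design.

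**What to change.** - In Table 1, make the share of patients attending at least 14 of 20 sessions the adherence outcome used for the verdict. Take all consented patients as the denominator, as the retention criterion does, and count each withdrawn patient on the sessions actually attended. Keep mean attendance and the completer-only figures as descriptive results, and limit footnote b to those.
- In Criteria for success, replace *attributable* with Table 1's causality term, so that the criterion covers serious events related or possibly related to the intervention or study procedures.
- Reconcile the notification wording in Safety reporting with that term, subject to the sponsor's policy.
- Put the thresholds in Table 1, or correct the sentence that says they are there.

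No new data, patients or procedures are needed. The adherence criterion becomes slightly harder to meet where non-completers attend less, and so does the safety criterion. The article requires modifications to be agreed by the research team and sponsor and approved by the ethics committee, so the change should be made before outcome data are reviewed.

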## Methods

### Study design

TELEX-Liver Cancer is a prospective, single-site, single-arm, pretest-posttest feasibility trial. In addition to receiving standard care, patients will receive a 10 week, home-based, virtual, group exercise intervention delivered in real time by an experienced physiotherapist. Feasibility and acceptability of the intervention and outcome measures will be assessed using a mixed-methods approach. A schematic diagram of the study schedule is presented in Fig. 1. The study is prospectively registered on the International Standard Randomised Controlled Trial Number (ISRCTN) registry (ISRCTN14411809). A Standard Protocol Items: Recommendations for Interventional Trials (SPIRIT) checklist [24] is in the supplementary files.

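### The safety outcome leaves out adverse events judged unrelated, although all events are recorded and a single-arm trial has no background rate against which to check that judgement

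*Protocol article*

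**What the plan says.** The relevant statements in the protocol article are:

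- **Outcome (Feasibility, Table 1).** Safety is "The number and type (i.e. serious or non-serious) of adverse events that are related or possibly related to the intervention or study procedures".
- **Who rates (Safety reporting).** One member of the research team "will be responsible for determining the attribution and seriousness of adverse events and ensuring they are appropriately documented". The section places adverse event reporting under the hospital trust's own policy for studies that are not drug trials; that policy is not reproduced.
- **What is recorded (Safety reporting).** "All adverse events will be recorded in the Trial Master File". Collection runs from consent to the 10-week follow-up.
- **What is reported onward (Safety reporting).** "We will report serious adverse events that are deemed to be related to study participation to the trial sponsor and the relevant research ethics committee".
- **Success criterion (Criteria for success).** "No serious adverse events are attributable to the intervention or study procedures".
- **Design (Study design).** "TELEX-Liver Cancer is a prospective, single-site, single-arm, pretest-posttest feasibility trial".

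**The concern.** Safety is one of the trial's stated aims, and the results are meant to inform a later randomised trial. The defined outcome passes every event through a causality rating before it is counted. Such ratings are hard to make when patients have an illness that produces events of its own. The Introduction describes age-related comorbidity, frailty and fluctuating symptoms of chronic liver disease. A control arm would show how many events occur without the intervention; here there is none. If a harm of the intervention were taken for background illness, it would be missing from the reported outcome, and a reader would have no all-cause count from which to form a different view. Planners of the later trial would want all-cause deaths, admissions and falls during the exposure period, and the outcome as defined does not supply them.

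**Working it through.** The plan states no safety rate, limit or probability, so there is no safety figure to reproduce. The only planned number needed is the sample of 20 from Sample size. Its own inputs support it: 3 eligible patients per week × 26 weeks × 0.30 consenting = 23.4, consistent with a target of at least 20.

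**Step 1. Follow one serious event through the plan, by its rating.**

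| Rating | Recorded (Safety reporting) | In the Table 1 outcome | Stated onward reporting (Safety reporting) | Counts against the success criterion |
|---|---|---|---|---|
| Related | Yes | Yes | Yes | Yes |
| Possibly related | Yes | Yes | Unclear | Unclear |
| Unrelated | Yes | No | None stated | No |

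The bottom row is the main point: the event is collected but is outside the outcome. The middle row is a separate problem of wording. Table 1 explicitly includes possible relation. Safety reporting speaks only of serious events "deemed" related in the sense of "We will report serious adverse events that are deemed to be related to study participation to the trial sponsor". The criterion uses a third term, "No serious adverse events are attributable to the intervention or study procedures". Nothing says whether the second and third include possible relation.

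**Step 2. How much hangs on one rating.** The criterion requires zero attributable serious events, so one rating in one patient decides it: 1/20 = 5% of the sample.

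**Step 3. Illustration of dependence on the rating.** Let p be the true risk per patient of a related serious event and s the chance that such an event is rated as attributable. Both are assumptions; the documents give neither. With independent patients, the probability of meeting the criterion is (1 − p × s)^20.

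| | s = 1 | s = 0.75 | s = 0.5 | s = 0.25 |
|---|---|---|---|---|
| p = 5% | 0.95^20 = 36% | 0.9625^20 = 47% | 0.975^20 = 60% | 0.9875^20 = 78% |
| p = 10% | 0.90^20 = 12% | 0.925^20 = 21% | 0.95^20 = 36% | 0.975^20 = 60% |

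At p = 10%, recognising only half of the related events triples the chance of a favourable verdict, from 12% to 36%.

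**Step 4. What zero events would show even with perfect rating.** The one-sided 95% upper limit for 0 of 20 is 1 − 0.05^(1/20) = 13.9%. The criterion is therefore limited evidence on its own, which is a further reason to show all the events beside it.

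**The case against.** A reader might infer that the safety verdict rests on an unreviewed judgement, and that unrelated events are hidden from everyone outside the team. The documents do not support either inference. The article says who is responsible for the rating; it does not say that nobody checks it. The trust's policy and the full protocol are not shown and may provide for review. Saying which events are actively reported also does not mean that the sponsor cannot see the rest. The sponsor is the same trust that monitors these patients.

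Four further points are fair, and they stand:

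- The filter is wider than strict causality. Because possibly related events count, a plausible alternative cause does not by itself exclude an event.
- Information is not lost. All events are recorded, the facilitator documents events at every session, and reasons for withdrawal, non-adherence and dropout are to be examined. Some unrelated deaths or admissions would therefore surface elsewhere in the report.
- The poor prognosis in the Introduction describes liver cancer in general. Participant eligibility selects treated patients with response or stable disease, preserved liver function, performance status 0 or 1 and a life expectancy of at least 6 months. No background serious-event rate for this group can be taken from the documents.
- An all-cause table would not change how the zero-event criterion behaves, and 20 uncontrolled patients cannot separate harm from background.

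None of this removes the core point. The other routes are partial: they cover events that end participation or explain missed sessions, not all events. The table is worth having because it shows what the rating was applied to, even though it cannot establish cause.

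**Conclusion.** The point holds as a cheap improvement. By explicit definition, the safety outcome omits events judged unrelated, although the plan already collects them. The rating that decides inclusion is given to one person with no second assessment described, and the single-arm design provides no comparator with which to test it. The number of events affected cannot be estimated from the documents. The percentages for meeting the criterion rest wholly on assumed values of p and s and show only the direction and possible size of the dependence. The ambiguity over possibly related serious events needs no assumption: it follows from setting the three wordings side by side. The documents do not show that the rating is wrong, that it goes unchecked, or that events are concealed.

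**What to change.** Redefine the Table 1 safety outcome as all adverse events recorded from consent to the 10-week follow-up, tabulated by seriousness and by attribution (related, possibly related, unrelated). Show deaths, unplanned admissions and falls irrespective of attribution. The article already has usable definitions: death and unplanned hospitalisation are in its definition of a serious adverse event, and a fall is defined under Exercise intervention. Keep the success criterion based on attributable events.

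Reconcile the attribution wording in Table 1, Safety reporting and Criteria for success, so that it is clear whether a serious event rated possibly related counts against the criterion and whether it falls under the stated onward reporting.

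The cost is one more table and one clarified definition. No new data are needed, because every event is already recorded. The downside is that unrelated disease events will appear in the safety table and need a sentence of context.
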